#### Secondary and exploratory endpoints

3.8.2

The secondary endpoint is fatigue, quantified by the FACIT-Fatigue survey, which assesses 7-day fatigue and is a recommended measure for adults with ESKD [4,38]. FACIT-Fatigue will be evaluated at baseline, week 6, and end of study. Fatiguability will be evaluated with the Pittsburgh Fatiguability Scale, a survey of expected physical and mental tiredness related to various activities [39]. Self-reported sleep quality will be measured with the PROMIS Sleep questionnaire [40]. Pain will be assessed using the PROMIS Pain Intensity and Interference questionnaires [41]. The SF-36 will be used to evaluate self-reported quality of life [42]. Self-efficacy for physical activity will be evaluated using a scale assessing readiness for change to increase physical activity [43]. Given the influence of patient activation on behavior [44,45], the Patient Activation Measure (PAM-13) will be evaluated [46,47]. Since the board described fatigue as a mind-body symptom, we will examine the Whole Person Health Index (WPHI), a self-assessed holistic view of one's health [48].

In addition to questionnaires, we will evaluate daily physical activity and inactivity (e.g., METs, steps, sedentary time, sleep, etc.) as well as sleep quality via accelerometer at baseline and end of study with 1 week wear of the ActiGraph (GT3X), a validated measure of activity and sleep quality that has been used with adults with ESKD [[49], [50], [51]]. Participants will fill out a log while wearing the ActiGraph to report sleep and non-wear times. A minimum of 5 valid days of wear will be included, and a valid day will be considered at least 8 h of wear time, which has been established as an acceptable parameter for reliability [52]. The sampling rate of the devices will be 30 Hz (Hz). For analysis, epoch length will be set to 10 s. Bout parameters and METs will be evaluated using the Freedson (1998) and Freedson EE algorithms [53]. As per other work using the ActiGraph in adults with ESKD, the cut points for analysis will be defined as < 100 counts/min for sedentary time, 100 to 1951 counts/min for light physical activity, and ≥1952 counts/min for moderate-to-vigorous physical activity (MVPA) [54].

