### Data analysis

3.9

The study hypothesis is that the recruitment ratio (percent of approached individuals who agree to participate) will be >60%, retention (percent of randomized individuals who complete the final 12-week study assessment) will be >80%, and adherence among retained participants (at least two progressive muscle relaxation sessions/step goal achieved per week; text messages read) will be >70%. We hypothesize that greater than 80% of retained participants will rate the study as acceptable (rating of agree or higher on end of study acceptability questions). Feasibility metrics and baseline descriptive statistics will be summarized. We will evaluate acceptability via Likert-scale, visual analogue scale, and open-ended questions. Mean scores will be calculated, and scores in the range from disagree to strongly disagree will be considered unacceptable conditions. Open-ended question answers will be summarized by the PI, and the summary will be reviewed by a research team member to verify accuracy. Adherence will be evaluated via fitness watch (steps) and number/duration of accesses on the website. Additionally, steps will be evaluated via accelerometer. Text message adherence will be assessed based on messages sent and read.

We will then estimate within group variability of change in the secondary outcome measure (FACIT-Fatigue) to appropriately power the future, fully powered trial informed by this feasibility trial. We will estimate correlation structure between the secondary outcome measure and Kt/V, dialysis fluid removal, dialysis dose, blood pressure and heart rate, change in blood pressure during treatment, number of missed dialysis treatments, medications, body mass index, weight, hemoglobin, albumin, and phosphorus to appropriately assess power for the future, full powered trial.

For missing data, we will use a complete case approach, as our preliminary work suggests low rates (<1%) of missing data. Multiple imputation methods will be used as sensitivity analyses to ensure robustness of findings if there is higher missingness than anticipated. We will monitor missing data and identify predictors of missingness, specifically evaluating demographic factors, including but not limited to age and sex, as predictors of missingness, and examine the acceptability of outcome measures to inform the future efficacy trial.

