#### Sample size

3.9.1

The sample size will consist of 40 participants, and we anticipate an attrition rate of no greater than 20% based on our team's previous work. This sample size will allow us to assess both feasibility and acceptability to a reasonable level of precision (estimating retention and intervention completion rates within a maximum range of error of 14%), achieve the necessary estimates to design a future, well-powered interventional trial, and it falls within well accepted guidelines on sample sizes for pilot studies of this type [55,56]. We will conduct Intention to Treat and Per Protocol Analyses [57].

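### The expected <1% missing data cannot justify complete-case analysis when the plan allows up to 20% attrition, and a complete-case set is not the promised intention-to-treat analysis

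*Protocol article*

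**What the plan says.** All references are to the protocol article.

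- **Data analysis (3.9), main method and its reason:** "For missing data, we will use a complete case approach, as our preliminary work suggests low rates (<1%) of missing data".
- **Data analysis (3.9), fallback:** "Multiple imputation methods will be used as sensitivity analyses to ensure robustness of findings if there is higher missingness than anticipated".
- **Data analysis (3.9), retention hypothesis:** "retention (percent of randomized individuals who complete the final 12-week study assessment) will be >80" per cent.
- **Sample size (3.9.1), attrition:** "The sample size will consist of 40 participants, and we anticipate an attrition rate of no greater than 20% based on our team's previous work".
- **Sample size (3.9.1), analysis populations:** "We will conduct Intention to Treat and Per Protocol Analyses".
- **Secondary and exploratory endpoints (3.8.2):** "FACIT-Fatigue will be evaluated at baseline, week 6, and end of study".

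The Data analysis section gives the within-group variability of FACIT-Fatigue change as the quantity that will be used to power the later trial. It also commits to monitoring missing data and looking for its predictors.

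**The concern.** The article gives one reason for complete case: hardly anything will be missing. Its own attrition figure is at least 20 times larger. Dropouts are the main source of missing week-12 scores, and the stated reason does not cover them.

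Two things are at stake. The first is the planning SD of FACIT-Fatigue change. Complete case discards the baseline and week-6 scores of anyone lost between week 6 and week 12. If leaving is related to fatigue, the completers' change and its spread may not represent the randomised group. The article makes such a link plausible: the patient board said that fatigue made one not want to do things, and named health status and mood as barriers to engagement (Formative work results, 2.1). The second is the label. An analysis that drops randomised participants for lack of an outcome is not intention-to-treat in the usual sense, and the article does not say how the two commitments fit together.

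**Working it through.** **Inputs from the article:** N = 40; attrition at most 20%; retention hypothesis above 80%; missing data below 1%; 1:1 allocation; FACIT-Fatigue at baseline, week 6 and week 12.

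**1. The plan's own precision figure.** The Sample size section gives a maximum error of 14% for retention and completion rates, without stating the confidence level, proportion or n. The 95% half-width is 1.96 × √(p(1−p)/n).
- p = 0.80, n = 32: 1.96 × √(0.16/32) = 13.9%.
- p = 0.70, n = 40: 1.96 × √(0.21/40) = 14.2%.

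Both round to 14%. The first would fit a plan that counts on 32 completers, but that is inference. The point does not depend on it.

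**2. Participants without a week-12 change.**
- At the attrition ceiling: 0.20 × 40 = 8 missing and 32 left, about 16 per arm if losses are balanced.
- If the retention hypothesis is met: strictly more than 80% of 40 is at least 33 retained, so at most 7 are missing.
- At the rate used as justification: below 0.01 × 40 = 0.4.

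**3. Can both figures describe week-12 missingness?** With a true rate of 1%, the binomial probability of 8 or more missing among 40 is about 6 × 10⁻⁹. They must describe different quantities, or one of them is wrong.

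**4. Loss of precision alone.** The 95% interval for an SD, as a multiple of the estimate, is √(df/χ²) at the 97.5% and 2.5% points. Pooled over arms (df = n − 2):
- n = 40: 0.82 to 1.29.
- n = 32: 0.80 to 1.34.

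This is a modest cost.

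**5. Possible bias, under assumptions that are not in the documents.** Suppose the lost 20% are those lowest on a normal variable that has correlation ρ with FACIT-Fatigue change. Removing the lowest 20% of a standard normal leaves variance 0.583 and shifts the mean by 0.350. For change, in units of its true SD, the completers' variance is 1 − 0.417ρ² and the mean shift is 0.350ρ.

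| ρ | completers' variance | SD too small by | future n too small by | mean shift (SD) |
|---|---|---|---|---|
| 0.3 | 0.96 | 2% | 4% | 0.10 |
| 0.5 | 0.90 | 5% | 10% | 0.17 |
| 0.7 | 0.80 | 11% | 20% | 0.24 |

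If dropout is unrelated to FACIT-Fatigue change (ρ = 0), there is no bias.

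**6. How much of that would a missing-at-random method recover?** The mechanism of step 5 was simulated with every dropout given a week-6 score, which is generous, and an assumed correlation of 0.6 between week-6 and week-12 change. True variance is 1.
- ρ = 0.5: about 0.89 for complete case, 0.91 for the missing-at-random estimate.
- ρ = 0.7: about 0.79 for complete case, 0.81 for the missing-at-random estimate. The mean shift falls from 0.24 to 0.17 SD.

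Under this mechanism most of the variance bias remains.

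**The case against.** **The <1% may mean item-level missingness among people who are assessed.** That is possible, and the text does not settle it. The two figures would then not conflict as forecasts. But on that reading the <1% says nothing about dropouts, so complete case for them has no stated justification.

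**Multiple imputation is already planned.** It is, and this softens the point. A reader might infer that the trigger is ambiguous because the article holds two anticipated values, <1% and 20%. The wording does not support much of that. The condition directly follows the <1% sentence, which is its natural antecedent, and one participant lost (1/40 = 2.5%) would already meet it. What stands is that imputation remains a conditional sensitivity analysis, while the main estimate still comes from completers.

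**This is a feasibility trial.** This stands as a limit on importance. Feasibility and acceptability are primary, and retention is computed on all randomised participants. No between-arm test of FACIT-Fatigue is described, and the Discussion disclaims efficacy. The mean shift in the table therefore feeds no stated inference. The intention-to-treat sentence is not tied to FACIT-Fatigue by name, and the article does not say whether change runs to week 6 or week 12. The loss of up to 8 applies to week 12.

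**The bias figures assume informative dropout, and sampling error is larger.** Both are true. At n = 40 the 95% interval for the variance runs from 0.67 to 1.66 times the estimate (0.817² and 1.289²), which is wider than a 4% to 20% bias.

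**Model details belong in the analysis plan.** Agreed. Their absence is not part of this point. The point is the reason that the article does state.

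**Conclusion.** The point holds. The <1% figure cannot justify complete case for participants who leave before week 12, nothing in the article reconciles it with the 20%, and a completers-only set does not meet the intention-to-treat commitment.

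The size is up to 8 of 40 without a week-12 change, or at most 7 if the retention hypothesis is met. Eight is a ceiling and should not be read as the expected loss. A reader might also infer that the planning SD will be understated. The documents do not establish that, since it requires dropout related to FACIT-Fatigue change. The 4% to 20% shortfall in future n, for assumed correlations of 0.3 to 0.7, illustrates the possible bias and is not the gain from the fix.

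The retention endpoint is unaffected, and the outcome concerned is secondary. This should be fixed, but it does not threaten the trial's main purpose.

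**What to change.** 1. Limit the <1% statement to item-level missingness among people assessed, or delete it. State how it relates to the 20% attrition figure.
2. Estimate FACIT-Fatigue change and its within-group variability with a method that keeps randomised participants who have partial data. Either a likelihood-based repeated-measures model on baseline, week 6 and week 12, or multiple imputation using arm, baseline and week-6 FACIT-Fatigue, would do.
3. Run multiple imputation whatever the observed missingness.
4. Keep complete case as a supportive analysis and do not label it intention-to-treat.

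The cost is a few sentences and a little extra programming, with no new data. The downside is reliance on missing at random: if dropout depends on unobserved fatigue, bias is reduced only partly, so the planning SD should be reported with that caution.

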#### Sample size

3.9.1

The sample size will consist of 40 participants, and we anticipate an attrition rate of no greater than 20% based on our team's previous work. This sample size will allow us to assess both feasibility and acceptability to a reasonable level of precision (estimating retention and intervention completion rates within a maximum range of error of 14%), achieve the necessary estimates to design a future, well-powered interventional trial, and it falls within well accepted guidelines on sample sizes for pilot studies of this type [55,56]. We will conduct Intention to Treat and Per Protocol Analyses [57].

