### Randomization

3.3

Participants will be randomized after consent and baseline testing are completed. The REDCap randomization module will be designed by the study statistician. Randomization will be stratified based on baseline fatigue scores as measured by the Functional Assessment of Chronic Illness Therapy-Fatigue (FACIT-F) scale (FACIT-F score <30 vs. **≥**30). Randomization within each stratum will be 1:1 to each of the two groups, utilizing a block randomization scheme (block size 4). The study statistician will create this allocation schedule.

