#### Primary endpoint

3.8.1

The primary study endpoints are feasibility and acceptability. We will examine recruitment, enrollment, and attrition metrics. We will measure adherence to the intervention, defined as participating in at least two progressive muscle relaxation sessions per week, which will be evaluated via individual login accesses and duration of each access to the study website, and having at least two days per week where they met their step goal, evaluated via the fitness watch. We will evaluate adherence to the text messages by evaluating number of messages read compared to the number of messages sent. We will also evaluate acceptability via Likert scale, visual analogue scale, and open-ended questions. Additionally, intervention participants will have the option to participate in an optional 1:1 interview to further explore acceptability of the intervention at the end of the study.

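### The 14% maximum error fits rates pooled over both arms near the plan's targets, but not intervention completion if that is measured in the one arm of about 20

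*Protocol article*

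**What the plan says.** All references are to the Protocol article.

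- **Sample size (3.9.1):** the total is fixed in the words "The sample size will consist of 40 participants". On dropout, the expectation is stated as "we anticipate an attrition rate of no greater than 20% based on our team's previous work". The precision claim is "estimating retention and intervention completion rates within a maximum range of error of 14" per cent. The confidence level, the assumed rate and the denominator are not given. The same sentence also rests the sample size on estimates for a future trial and on published guidelines for pilot studies.
- **Randomization (3.3):** "Randomization within each stratum will be 1:1 to each of the two groups".
- **Data analysis (3.9):** the targets are "retention (percent of randomized individuals who complete the final 12-week study assessment) will be >80" per cent, "adherence among retained participants (at least two progressive muscle relaxation sessions/step goal achieved per week; text messages read) will be >70" per cent, and that "greater than 80% of retained participants will rate the study as acceptable".
- **Primary endpoint (3.8.1):** "adherence to the intervention, defined as participating in at least two progressive muscle relaxation sessions per week", together with meeting the step goal on at least two days a week.
- **Interventions (3.5) and Text messages (3.5.1):** the control arm is taught to read nutrition labels and has no relaxation or step component. Text messages go to both arms.

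Intervention completion, one of the two rates to which the 14% is attached, is not defined and is not among the metrics listed under Primary endpoint or Data analysis.

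**The concern.** One error figure is given for two rates that need not share a denominator. Retention is a proportion of all 40 randomised. Completion of Fight Fatigue can be observed only in those allocated to it, about half of the 40. Halving the denominator multiplies the half-width by √2, or about 1.41, so a figure that suits the whole trial cannot also suit one arm at the same rate.

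This is the only numerical precision statement for the primary endpoints. If 14 of 20 intervention participants completed (70%), someone relying on ±14% would read 56% to 84%, while the exact 95% interval is 45.7% to 88.1%. The lower limit, which bears on whether to proceed to a full trial, would be about 10 percentage points too favourable.

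**Working it through.** **Inputs.** 40 randomised and at most 20% attrition (Sample size); 1:1 allocation (Randomization); targets of 80% for retention, 70% for adherence and 80% for acceptability (Data analysis). The derived denominators are:

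- retained, both arms: 40 × 0.8 = 32
- intervention arm randomised: 40 / 2 = 20
- intervention arm retained: 20 × 0.8 = 16

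The 95% level is my assumption.

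**Formula.** Half-width = 1.96 × √(p(1 − p)/n).

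**Step 1: reproduce the plan's figure.**

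- n = 40, p = 0.70: 1.96 × √(0.21/40) = 14.2%
- n = 32, p = 0.80: 1.96 × √(0.16/32) = 13.9%

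Both agree with 14%, and both use denominators pooled over the arms. The article does not say which derivation was used.

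**Step 2: retention, the named rate with a clear denominator.** n = 40, p = 0.80: 1.96 × √(0.16/40) = 12.4%, inside 14%.

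**Step 3: 14% as a worst case over every rate.** n = 40, p = 0.50: 1.96 × √(0.25/40) = 15.5% (Wilson 14.8%, exact 16.2%). A worst case of 14% would need 1.96² × 0.25/0.14² = 49 participants. At the 90% level the n = 40 worst case is 13.0%.

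**Step 4: the intervention arm.**

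| Denominator | p = 0.70 | p = 0.80 | Maximum (p = 0.50) |
|---|---|---|---|
| All randomised, n = 40 | 14.2% | 12.4% | 15.5% |
| All retained, n = 32 | 15.9% | 13.9% | 17.3% |
| Intervention arm, n = 20 | 20.1% | 17.5% | 21.9% |
| Intervention arm retained, n = 16 | 22.5% | 19.6% | 24.5% |

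**Step 5: does another convention rescue 14% in the arm?**

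- Wilson, 95%, at 70%: 18.7% (n = 20) and 20.5% (n = 16).
- Same formula at the 90% level, at 70%: 16.9% and 18.8%.
- Same formula at the 90% level, at 80%: 14.7% and 16.4%.
- A 95% half-width of 14% requires a rate of at least 88.5% with n = 20, or 91.0% with n = 16.
- At a rate of 70% it requires 1.96² × 0.21/0.14² = 41.2, so 42 people in the intervention arm, more than the whole trial.

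**Step 6: what this means beside a threshold.** Adherence of 12/16 (75%) would meet the 70% target, with a Wilson 95% interval of 50.5% to 89.8%.

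**The case against.** Five points can be made for the plan.

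1. **The targets are floors.** Above 50% the half-width shrinks as the rate rises. So 14.2% is the largest error at n = 40 for any rate of 70% or more, and 13.9% is the largest for any rate of 80% or more with 32 retained. Read this way, the word maximum is coherent for pooled rates. This stands.
2. **The 95% level is assumed.** At 90%, n = 40 stays within 14% at every rate (13.0% at worst, without continuity correction). This also stands for pooled rates. It does not help the intervention arm (Step 5).
3. **Intervention completion is undefined.** Both conditions are described under Interventions, and both consist of two scripted sessions followed by texts. Completion of assigned sessions could therefore be counted in all 40. This is possible, and under it the pooled denominator applies. It is the less natural reading, since the trial's intervention is Fight Fatigue and controls do not receive it.
4. **The 14% is not attached to adherence.** Correct. The n = 16 figures show the precision available for relaxation and step adherence; they do not contradict a claim made for it. Text-message adherence can use both arms.
5. **The article condenses a fuller protocol.** The level, assumed rate and denominator may be given there, so their absence alone is no fault. The point is that the printed figure is attached to a rate it does not fit on the natural reading.

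A reader might infer that 40 participants cannot deliver 14% at all, or that the justification for the sample size collapses. The document supports neither. The figure reproduces at the plan's own targets, retention is estimated more tightly than claimed, and precision is only one of three stated grounds for n = 40.

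**Conclusion.** The concern holds in a limited form. For pooled rates near the targets the 14% is sound, and the word maximum fails only if a 95% worst case over all rates is meant, by about 1.5 percentage points (15.5% against 14%).

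For intervention completion as an intervention-arm rate, the true error at the 70% to 80% level is 17.5% to 20.1%, or 1.25 to 1.43 times the stated figure (17.5/14 and 20.1/14). Relaxation and step adherence among the retained is wider still, at 19.6% to 22.5%.

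This rests on three assumptions: a 95% two-sided interval, an intervention-arm reading of an undefined term, and attrition at the plan's 20% ceiling, falling equally on both arms. The first is not critical: in the arm, the half-width at 70% or 80% exceeds 14% at the 90% level too. The second is critical: if completion is pooled over both arms, the 14% is acceptable near the targets and only the definition needs repair.

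**What to change.** Keep n = 40. In the Sample size section:

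- define intervention completion and its denominator;
- state the confidence level and the assumed rate;
- replace the single figure by one for each metric. At 95%, these would be:
  - retention (n = 40): within 12.4% at 80%, at most 15.5%;
  - intervention-arm completion (n = 20): within 20.1% at 70% and 17.5% at 80%, at most 21.9%;
  - relaxation and step adherence among retained intervention participants (about 16): within 22.5% at 70% and 19.6% at 80%, at most 24.5%.

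In the Data analysis section, commit to Wilson or exact 95% intervals beside each feasibility threshold, so that a point estimate just above its target is not read as firm evidence.

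The cost is a sentence or two of text and a less favourable precision statement. No extra participants, data collection or design change are needed.
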